The llluminOss® System is the first percutaneous, patient-specific, fracture stabilization system [16]. Only a small and percutaneous incision is required to insert an inflatable balloon into the medullary canal. The balloon, which spans the fracture is infused with a light curable monomer. The monomer hardens in situ by applying a visible light, resulting in a stable and patient-specific implant that provides longitudinal strength and rotational stability over the length of the implant. Early functional after-treatment without additional plaster immobilization is possible. The latter is considered the main strength of this device over non-operative treatment and conventional metal implants [16].

The IO-WRIST study is designed to determine results after treatment with IlluminOss®. Outcome will be monitored as propagated by the distal radius working groups of the International Society for Fracture Repair and the International Osteoporosis Foundation [17]. This study primarily aims to examine the effect of operative treatment using the IlluminOss® System on the DASH (Disabilities of the Arm, Shoulder, and Hand) score in elderly patients who sustained a unilateral, displaced, extra-articular distal radius fracture. Secondary objectives are to examine the effect on functional outcome, the level of pain, health-related quality of life, the time to regaining independence in activities of daily living (ADL), the resumption of work/ADL, range of motion of the wrist, the time to radiographic healing, the rate of complications with associated secondary interventions, and the costs for health care use and lost productivity.

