Radiographic evaluation will be done using routinely obtained radiographs. The degree of radial inclination, volar/dorsal tilt and ulnar variance, the amount of comminution, and the radial length will be measured directly in the digital Picture Archiving and Communication System (PACS) of the participating hospital on standard AP, lateral carporadial, or lateral wrist X-rays. Radiographs will be made using a standardized protocol; 1) for the AP radiographs, the shoulder should be held in 90° abduction, the elbow in 90° flexion, and the wrist in neutral position; 2) for the lateral X-rays, the shoulder should be held in a neutral position and the elbow in 90° flexion; 3) for the lateral carporadial radiographs, the lower arm should be positioned on a 20–25° angled wedge.

Radiographic healing and alignment of the distal radius will be evaluated using X-rays. The treating physician and two independent experts will assess the Lidström score for the repeated X-rays of the wrist blinded from the first assessment [36]. X-rays will be blinded and radiographic evaluation will be done by two experts independently. Any discrepancy will be resolved in a consensus meeting.

The following complications will be collected from the patients’ hospital records; 1) skin problems (threatened skin, necrosis); 2) Surgical site infection [37]; 3) radial nerve pathology; 4) vascular injury (hemorrhage, injury to the radial or ulna artery); 5) tendon pathology (abductor pollicis brevis/longus, extensor carpi radialis brevis/longus, extensor pollicis longus); 6) compartment syndrome; 7) secondary dislocation (loss of length, angulation, or rotation); 8) implant failure (balloon breakage); 9) non-union/pseudarthrosis (i.e., no healing or progress towards healing visible at 6 months after surgery); 10) malalignment severe enough to treat surgically; 11) CRPS type I; 12) systemic, generic or other complications.

Secondary intervention within 1 year of surgery will be collected from the patients’ hospital records. Only interventions aimed at relieving pain, treating infection, promoting fracture healing, or improving function will be recorded. They will be categorized as 1) drug treatment (oral or intraveneous antibiotics, other); 2) surgical treatment (incision and drainage, revision osteosynthesis (plate osteosynthesis, intramedullary nail or other), implant removal, other).

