### Study procedures

Patients will be followed for 1 year. Follow-up visits are scheduled at 2 weeks, 6 weeks, 3 months, 6 months, and 12 months after index surgery. These visits are standard of care for patients with a distal radius fracture. Table 1 shows an overview of the follow-up schedule, including the accepted windows around each visit.

**Table 1 Tab1:** Schedule of events

Radiographs & Events	Screening	Enrolment	Baseline	Per/Post	2 weeks	6 weeks	3 months	6 months	12 months
				surgery	(10–16 days)	(5–7 weeks)	(11–15 weeks)	(5–7 months)	(12–14 months)
X-Ray^a^	X				(optional)	X	X	X	(optional)
Screening	X								
Informed Consent		X							
Baseline Data			X						
Surgical Report Form				X					
Clinic FU					X	X	X	X	X
Range of Motion					X	X	X	X	X
DASH					X	X	X	X	X
PRWE					X	X	X	X	X
Pain (VAS)					X	X	X	X	X
SF-36					X	X	X	X	X
EQ-5D					X	X	X	X	X
ADL independence					X	X	X	X	X
Work/ADL resumption					X	X	X	X	X
Complications					X	X	X	X	X
Secondary Interventions					X	X	X	X	X
Health Care Use					X	X	X	X	X
Early Withdrawal					^b^	^b^	^b^	^b^	^b^

^a^The AP and lateral X-rays will be used for determining radiographic healing

^b^Only applicable at time of withdrawal

During these regular clinical follow-up visits, AP and lateral radiographs are made for determining radiographic healing and malalignment.

At each planned visit, the clinical investigator (or a research assistant) will document complications and secondary interventions, and will check information within the patients’ hospital files. At the last visit, all planned secondary interventions will also be recorded.

At each planned visit, a physician, clinical investigator, or research assistant will measure the range of motion of the wrist using a goniometer. In addition, patients will be requested to complete a set of questionnaires (DASH, PRWE, VAS for pain, SF-36, EQ-5D, ADL/work, health care consumption, and production loss).

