### Sample size calculation

For case series, a generally accepted assumption is that introducing and implementing a (relatively new) surgical technique requires 30 patients [39]. A formal sample size calculation for this study is based on the DASH score (primary outcome measure). The minimal important change for the DASH score is 10 points [19]. Based on literature data we expect a mean DASH of 23 (SD 19) in non-operatively treated patients [40, 41]. In order to detect a 10-point improvement (mean 13, SD 10) in patients treated with IlluminOss® with a two-sided α of 0.05 and a 90 % power (β = 0.10), at least 38 patients are needed. Anticipating 10–15 % loss to FU and 10 % mortality, 50 patients will be enrolled.

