### Statistical analysis

The Statistical Package for the Social Sciences (SPSS) version 21 or higher (SPSS, Chicago, Ill., USA) will be used for statistical analysis. The STrengthening the Reporting of OBservational studies in Epidemiology (STROBE) guidelines will apply to data reporting. If necessary, missing values will be replaced using multiple imputation following the predictive mean matching method, using ten imputations. The Shapiro-Wilk test will be used for testing normality of continuous data. All statistical tests will be two-sided, and a p-value <0.05 will be used as threshold of statistical significance.

Descriptive analysis will be performed in order to report baseline and outcome data. Data will be reported as mean with SD (continuous, parametric data), as median with first and third quartile (continuous, non-parametric data), or as number with frequency (categorical data). A Wilcoxon Signed Rank test will be applied for comparing continuous outcome scores at 1 year with those at their first measurement.

Depending on the variability of covariates, multivariable analysis may be performed. A linear mixed-effects regression model will be made to model the relation between specific covariates and the outcome measures that are recorded repeatedly (i.e., DASH and other PROMs). This multilevel model will include fixed effects for covariates like involvement of the dominant side, gender, and age if deemed necessary. These confounders will be selected based upon literature data and by eyeballing the descriptive statistics. The beta values will be reported with their 95 % confidence interval and p-value. Estimated marginal mean will be computed and reported per follow up moment.

For the continuous data determined only once (e.g., time to radiographic healing), a multivariable linear regression model may be developed, with the outcome measure as dependent variable. Potentially confounding variables will be entered as covariate. Beta values will be reported with 95 % confidence interval and p-value.

For the categorical data, a multivariable logistic regression model will be developed, with the outcome measure as dependent variable. Potentially confounding variables will be entered as covariate. Odds ratio’s will be reported with 95 % confidence interval and p-value.

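### Time to radiographic healing is treated as ordinary continuous data although it is interval- and right-censored, so its summary tends to run late and the optional linear regression is liable to bias

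*Protocol article*

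**What the plan says.** The Background lists healing time among the secondary objectives: "the time to radiographic healing, the rate of complications with associated secondary interventions". The Statistical analysis section takes it as its example of a continuous outcome measured once: "For the continuous data determined only once (e.g., time to radiographic healing), a multivariable linear regression model may be developed". For that model, "Beta values will be reported with 95 % confidence interval and p-value". Continuous outcomes are otherwise described by mean and SD, or by median and quartiles. The section names no method for censored times. Its one provision for absent values is multiple imputation by predictive mean matching, ten times, if needed.

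On observation, the Study procedures section states: "Follow-up visits are scheduled at 2 weeks, 6 weeks, 3 months, 6 months, and 12 months after index surgery", and "During these regular clinical follow-up visits, AP and lateral radiographs are made for determining radiographic healing and malalignment". Table 1 requires X-rays at 6 weeks, 3 months and 6 months, with windows of 5–7 weeks, 11–15 weeks and 5–7 months. It makes them optional at 2 weeks and 12 months. The Outcome measures section relies on routine radiographs and lists non-union as a complication, defined as "no healing or progress towards healing visible at 6 months after surgery". The Sample size calculation section allows for 10–15% loss and 10% "mortality, 50 patients will be enrolled".

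**The concern.** A fracture first seen healed on the 3-month X-ray healed at some point since the 6-week film. The plan has no way to record that interval, so the date of the film is the natural value to enter as the healing time. The gaps between required X-rays are about 7 weeks (6 to 13) and 13 weeks (13 to 26), which is large against the quantity being measured.

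Patients never seen healed have no value at all. Leaving them out removes the slowest healers and pulls the mean down. Imputing them by predictive mean matching copies dates observed in other patients. That gives a healing time to someone who died or did not unite, and it cannot exceed the latest date observed. It also leaves the recorded visit dates as if they were exact.

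At stake are the reported healing time, which enters the descriptive results even if no model is fitted, and the covariate effects and intervals if the regression is run.

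**Working it through.** **The plan's own figure.** The article gives no figure for healing time, so there is none to reproduce. Its one calculation, for the DASH, does reproduce: ((1.960 + 1.282) × 19/10)² = 37.9, so 38; and 38/(0.85 × 0.90) = 49.7, so 50. This point uses only the attrition assumed there.

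**Step 1: the late shift in the mean.** Assumptions, not from the article: healing times are gamma with shape 6 and median 6, 8 or 10 weeks, and X-rays fall at exactly 6, 13, 26 and 52 weeks. Each patient gets the date of the first X-ray at or after healing. True mean = 6 × median/5.670. Visit-dated mean = sum of (share first seen healed at each X-ray × week).

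| Median (wk) | True mean | Share at 6 / 13 / 26 / 52 wk | Visit-dated mean | Ratio |
|---|---|---|---|---|
| 6 | 6.35 | 0.500 / 0.483 / 0.017 / 0.000 | 9.72 | 1.53 |
| 8 | 8.47 | 0.2555 / 0.6412 / 0.1031 / 0.0002 | 12.56 | 1.48 |
| 10 | 10.58 | 0.1297 / 0.6145 / 0.2525 / 0.0033 | 15.50 | 1.47 |

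The mean is 47% to 53% too late. At most 0.33% heal after 26 weeks here, so the optional 12-month X-ray hardly matters in these scenarios.

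**Step 2: patients without a healing time.** Attrition is 20% to 25%, or 50 × 0.20 = 10 to 50 × 0.25 = 12.5 patients. Those who leave after a healed X-ray do have a time. If leaving is uniform over 52 weeks (an assumption), the expected number without one is 50 × attrition × visit-dated mean/52:

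- lowest: 50 × 0.20 × 9.72/52 = 1.9
- highest: 50 × 0.25 × 15.50/52 = 3.7

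Non-unions come on top; the article gives no rate.

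**Step 3: the regression.** Simulation with 50 patients and 300 runs per scenario. Healing times were lognormal (median 7, 9 or 12 weeks in the reference group, log-SD 0.4 to 0.6), with one binary covariate (time ratio 1, 1.5 or 2). X-rays fell within the Table 1 windows, and attrition was 0, 20 or 25% (20% only with a 12-month X-ray). All healing-time and covariate inputs are assumed. Ordinary least squares was fitted to the first X-ray date showing healing, leaving out patients never seen healed. Where the covariate had a real effect:

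| | 12-month X-ray taken | No 12-month X-ray |
|---|---|---|
| Bias in mean healing time | +19% to +49% | −12% to +46% |
| Bias in beta | −11% to +42% | −62% to +28% |
| Coverage of 95% CI | 85% to 97% | 4% to 96% |

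The worst case had median 12 weeks, time ratio 2, no attrition and no 12-month X-ray: beta was 5.39 weeks against a true 14.37 (5.39/14.37 = 0.375), with 4% coverage. With no covariate effect, beta was about 0 and coverage 94% to 97%, but the mean was still 40% to 49% too late.

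**Step 4: the alternative on the same data.** An interval-censored lognormal model gave mean log time ratios of 0.39–0.42 (true 0.405) and 0.67–0.71 (true 0.693), with coverage of 93% to 96% throughout. This flatters the alternative somewhat, because the fitted distribution was the one that generated the data.

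**The case against.** The strongest reply is that little rests on this model. The study is a single-arm case series, healing time is one secondary outcome, and the regression only may be developed. A beta computed from visit dates also keeps a plain meaning, as a difference in mean time to the first X-ray showing healing. All of that is correct and limits the weight of the point. It does not remove it: the descriptive summary carries the late shift whether or not a model is fitted, and the section names the outcome and assigns it an unsuitable method, so this is not detail left to another document.

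Several stronger readings are tempting but not supported.

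- A reader might infer that the estimates and intervals are bound to be wrong. The article gives no healing-time distribution, and coverage was near nominal in several assumed scenarios.
- A reader might count all 20–25% attrition as patients without a healing time. Those figures were set for the DASH sample over a full year; Step 2 shows why they are only an upper bound.
- A reader might see a contradiction between Table 1 and the sentence "During these regular clinical follow-up visits, AP and lateral radiographs are made for determining radiographic healing and malalignment". That sentence does not say every visit, whereas neighbouring paragraphs do say so where it is meant. The two can stand together.
- A reader might extend the point to time to ADL independence. The article does not assign that outcome to this model, and patients are asked for the time directly, so the visit-date shift does not carry over.

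**Conclusion.** The point holds in a limited form. Time to radiographic healing is interval-censored by the X-ray schedule and right-censored when healing is not seen, yet the article treats it as ordinary continuous data. Predictive mean matching does not correct this.

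The most consistent error is a late mean: about 50% under gamma medians of 6 to 10 weeks, and 19% to 49% in the lognormal scenarios with a 12-month X-ray. Without that X-ray, omission of slow healers can offset or reverse the shift. If the regression is fitted, its covariate effects are liable to bias and its intervals may be invalid. Severe failure arose mainly with slow healing and no 12-month X-ray. All these sizes rest on assumed healing times. The primary DASH analysis is unaffected, but the change is worth making because it is cheap.

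**What to change.** In the Statistical analysis section, take healing time out of the linear-regression paragraph and state instead:

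- Report the cumulative proportion healed at the 6-week, 3-month and 6-month X-rays, with 95% CIs and the denominator at each.
- If covariates are examined, use an interval-censored model or a discrete-time (complementary log-log) model. Each healing time enters as the interval between the last X-ray not showing healing and the first showing it. Unhealed patients are censored at their last available X-ray, including an optional one.
- Impute no healing time for non-union or death.
- If time to ADL independence is analysed as a time, use a time-to-event method with death as a competing event.

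The cost is revised wording and a few lines of code, with no new data. The downside is that effects are expressed as proportions, time ratios or hazard ratios rather than in weeks.

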## Background

Distal radius fractures are the second most common osteoporotic fractures [1]. The number of hospitalizations due to these fractures in The Netherlands in patients aged 50 years and older increased from 877 in 1997 to 2912 in 2009 [2]. In line with demographic developments, osteoporotic fractures including those of the wrist can be expected to increase further in the coming years, with a concomitant increased burden on health care resources [3–5].

The current standard treatment for patients with a displaced extra-articular distal radius fracture as mentioned in the Dutch treatment guideline is closed reduction and plaster cast immobilization for 4–6 weeks [6]. Non-operative treatment remains controversial due to high dislocation rates (36–57 %) and often disappointing functional recovery [6–11]. Immobilization may also induce stiffness. Multiple studies have shown that comminuted extra-articular distal radius fractures are characterized by instability, and plaster immobilization will usually not prevent substantial redisplacement [8, 12, 13].

Several operative procedures are used for extra-articular distal radius fractures. In osteoporotic bone, angular stable plates are widely used, whereas the interest in and use of intramedullary devices is growing. Potential advantages of modern intramedullary devices could be the minimal surgical exposure for introduction of the device and the low risk of implant-related soft tissue irritation. This includes a reduced risk of tendon injury and screw penetration into the joint, which are the main problems of volar plating [14]. A recent literature review showed that intramedullary nailing gives a comparable range of motion, functional outcome, and grip strength as other fixation techniques, however the 0–50 % complication rate may raise concerns about the role of intramedullary nailing [15]. In addition to injury of the superficial radial nerve as most common complication (occurring in 9.5 % of patients), irritation from metalwork, tenosynovitis, and infection occurred in 1-2 % of patients. New devices and surgical techniques should be aimed at reducing the risk of these complications.

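### Logistic models are planned for categorical outcomes with no condition on event counts, and at the article's own rates single complications are too rare to support them; mixed-model covariates are partly chosen by looking at the data

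*Protocol article*

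**What the plan says.** All the relevant analysis rules stand in the Statistical analysis section of the protocol article.

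- Multivariable work is introduced conditionally: "Depending on the variability of covariates, multivariable analysis may be performed".
- Repeated outcomes (DASH and the other patient-reported measures) get a linear mixed model with "fixed effects for covariates like involvement of the dominant side, gender, and age if deemed necessary". The selection rule follows in the same paragraph: "These confounders will be selected based upon literature data and by eyeballing the descriptive statistics".
- For continuous outcomes determined once, "a multivariable linear regression model may be developed, with the outcome measure as dependent variable".
- For categorical outcomes the verb is firmer: "For the categorical data, a multivariable logistic regression model will be developed, with the outcome measure as dependent variable". On covariates the paragraph says only: "Potentially confounding variables will be entered as covariate". Odds ratios are to be reported with 95% confidence intervals and p-values.
- On testing: "All statistical tests will be two-sided, and a p-value <0.05 will be used as threshold of statistical significance".

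The same section plans counts with frequencies for categorical data. The Outcome measures section lists twelve complication categories, plus secondary interventions by type. The Background gives literature rates for intramedullary nailing: 9.5% for "injury of the superficial radial nerve as most common complication", 1-2% for metalwork irritation, tenosynovitis and infection, and 0-50% for complications overall.

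**The concern.** A logistic model needs enough events to estimate its coefficients. With very few, a covariate or a combination of covariates often separates patients with the event from those without it. The maximum-likelihood odds ratio is then zero or infinite, and its interval and p-value mean nothing. The only condition in the plan concerns how much the covariates vary, not how many events occur. There is no minimum number of events, no limit on covariates and no sparse-data method. An analyst following the text could therefore produce unusable odds ratios for single complications.

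The second issue is separate. Part of the covariate choice for the mixed models rests on looking at the study's own descriptive data. If the analyst looks at how covariates relate to the outcome and keeps the promising ones, the reported p-values are too small and the intervals too narrow. This affects covariate effects on DASH, the primary outcome measure, though not its plain description.

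**Working it through.** **1. The plan's sample size.** A one-sample normal approximation with SD 19, difference 10, two-sided alpha 0.05 and 90% power gives (19 × (1.960 + 1.282) / 10)² = 37.9, so 38. Allowing for 15% loss and 10% mortality, 38 / (0.85 × 0.90) = 49.7, so 50. Both figures reproduce. They concern DASH; the article gives no event count for categorical outcomes.

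**2. Expected events** (patients × rate, with the Background's rates):

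| Outcome | Rate | 38 patients | 50 patients |
|---|---|---|---|
| Rarer single complication | 1% | 0.38 | 0.5 |
| Rarer single complication | 2% | 0.76 | 1.0 |
| Commonest single complication | 9.5% | 3.6 | 4.75 |
| Any complication | 0-50% | 0-19 | 0-25 |

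With 50 patients the binomial chance of no event at all is 0.99^50 = 61% at 1%, 0.98^50 = 36% at 2% and 0.905^50 = 0.7% at 9.5%. With three covariates, 4.75 events is 4.75 / 3 = 1.6 per covariate, and 25 events is 25 / 3 = 8.3.

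**3. How often finite odds ratios fail to exist.** This was simulated with 1,000 datasets per setting and a linear-programming check for separation; datasets without events count as failures. Assumptions not in the article: three covariates (the examples named for the mixed model), dominant side in 50%, 80-90% female, normally distributed age, and no true association.

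| Event rate | 38 patients | 50 patients |
|---|---|---|
| 1% | more than 99% | 98-99% |
| 2% | 97-98% | 93-97% |
| 9.5% | 61-76% | 46-67% |
| 20% | 23-46% | 14-37% |
| 36% | 6-29% | 3-17% |
| 50% | 4-23% | 0.5-13% |

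Each range runs from 80% to 90% female. The problem is severe for single complications and much smaller for a composite near the top of the 0-50% range.

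**4. What n/N with an exact interval would show.** Clopper-Pearson 95% limits: 0/50 gives 0 to 7.1%; 5/50 gives 3.3% to 21.8%. These exist for any count.

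**5. Covariate selection.** For illustration, 43 patients were simulated (an assumed number between 38 and 50) with independent null covariates and ordinary linear regression. With three covariates fixed in advance, the chance of at least one p<0.05 is about 13% (theory for independent tests: 1 − 0.95³ = 14%). Keeping the three most associated of K candidates gives about 30% for K = 8, 37% for K = 10 and 48% for K = 15. In a logistic version (50 patients, 30% event rate, best three of ten), the error per coefficient rises from 5.1% to 14.9%. The candidate pool and ranking by outcome are assumptions. The plan also uses literature data, so these figures mark the upper end.

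**The case against.** Several points on the other side stand.

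- A reader might infer that odds ratios would replace complication rates. They would not, because counts with frequencies are planned whatever happens to the models. Only an interval for them is unstated.
- A reader might call the logistic models mandatory. The logistic sentence is firm, but it follows the general statement that multivariable analysis may be performed. That softens the commitment; since it turns on covariate variability, it does not protect against sparse events.
- A reader might take every categorical outcome to have five events or fewer. The Background's overall range allows up to 25 for any complication, and the article does not say that each complication gets its own model.
- A reader might say that without a control group nothing can be confounded. The Intervention section collects surgical details to study their effect on outcome, so within-cohort associations are intended and can be confounded.
- A reader might carry the eyeballing rule over to the logistic models or treat it as the sole rule. It stands in the mixed-model paragraph beside literature data. It could also mean dropping covariates that hardly vary, which ignores the outcome and does not raise the false-positive rate.
- A reader might expect sparse events to produce too many small p-values. The reverse holds: at a 9.5% event rate, Wald tests of prespecified covariates had 1.6% error among models that could be fitted.

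It can also be said that such detail belongs in an analysis plan. That holds for the choice of sparse-data method, but the article itself fixes the model type, the reported quantities and the selection rule.

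**Conclusion.** The concern holds in limited form. The article commits to multivariable logistic models without regard to event counts. At its own literature rates, single complications would give about 0.4 to 5 events each. A three-covariate model would then almost always lack finite odds ratios at 1-2%, and would fail in roughly half or more of datasets at 9.5%. This rests on the assumed covariates and on nailing rates carrying over to this device. The article gives no rate for secondary interventions, so for them the point is only that no event condition exists. A composite of any complication might support a limited model.

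The mixed-model selection rule is a separate, conditional weakness: it raises the false-positive rate only if outcome associations are inspected, and its size depends on the candidate pool. The descriptive DASH result is unaffected. The change is worth making because it is cheap and both rules, applied as written, can give misleading inference.

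**What to change.** - Drop the logistic models for individual complications and secondary interventions. Report n/N with exact (Clopper-Pearson) 95% confidence intervals per category and for any event.
- Fit a logistic model only where events suffice, such as for any complication, for example Firth-penalised with a covariate fixed in advance.
- Fix the mixed-model covariates as the three already named (age, gender, dominant side), delete the reference to eyeballing, and label any other covariate analysis exploratory.

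This changes wording only and needs no further patients or data. The cost is fewer covariate results to report.
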